## Introduction

Friedreich’s ataxia (FRDA) is the most common inherited ataxia, with an estimated incidence in of 1 in 29,000 and a carrier frequency of 1 in 85 individuals of Caucasian background [1, 2]. Neurological features include progressive gait and limb ataxia, absent lower limb reflexes, extensor plantar responses, dysarthria and loss of position and vibration sense [3]. Non-neurological features include cardiomyopathy, visual and hearing impairments, diabetes mellitus, glucose intolerance and skeletal deformities [4]. Onset of FRDA occurs, on average, at 10–15 years, but may be delayed to the middle or later years of life.

The genetic cause of FRDA is mutation of the *FXN* gene, primarily in the form of homozygous GAA trinucleotide repeat expansions [5, 6]. The age of disease onset and associated severity of some symptoms is inversely correlated with the size of the GAA expansion on the smaller of the *FXN* alleles (GAA1) [7]. This genetic mutation results in reduced expression of frataxin, an essential protein in the Iron-Sulfur (FE-S) cluster complex, which disrupts iron homeostasis [8, 9]. Frataxin is highly expressed in the dorsal root ganglia (DRG), the spinal cord, cerebellar dentate nuclei, cerebral cortex, pancreas, heart, liver and skeletal muscle [5], reflecting the tissues most impacted in FRDA.

The neuropathology underlying FRDA is multifaceted and complex. Hypoplasia of large and small neurons of the DRG, as well as effects on the peripheral nerves and spinal cord are observed and suggests neurodevelopmental origin [10, 11]. Over time, atrophy of the dentate nucleus becomes apparent, significantly contributing to the neurological phenotype [10, 12, 13]. Abnormalities in cerebral structures [14–16], functions [17–20] and both intra-cerebral and cerebello-cerebral connectivity [17, 21–25] have also been reported in individuals with FRDA.

Currently, there are no approved disease-modifying treatments for FRDA. Trials to investigate new drugs typically employ broad measures of clinical and functional progression, which require large sample sizes and long observational periods to detect therapeutic efficacy [26–29]. Useful biomarkers that can more rapidly and sensitively identify tissue-specific effects, thus improving clinical trial efficiency, are therefore urgently required to enable early decision making and to support potential regulatory considerations.

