#### Inclusion and exclusion criteria

Participants with FRDA are eligible for TRACK-FA if they meet the inclusion and exclusion criteria as outlined in Table 1. Due to the nature of this criteria, this study is only targeting those individuals with FRDA that are largely ambulant and in the first 25 years of disease duration.

**Table 1 pone.0269649.t001:** Inclusion and exclusion criteria used for the enrolment of FA participants into the TRACK-FA study.

Inclusion criteria below	Exclusion criteria below
Age ≥ 5 years	Acute or ongoing medical or other conditions not attributed to FRDA
Biallelic GAA repeat length > 55 in intron 1 of *FXN* and/or GAA repeat length > 55 in intron 1 of *FXN* in one allele and another type of mutation that is inferred to cause loss of function in the second *FXN* allele	Other neurological condition apart from FRDA
Age of disease onset ≤ 25 years	MR contraindications (e.g., pacemaker or other metallic surgical implants)
Disease duration ≤ 25 years	Presence of metallic dental braces (creates unwanted artifacts)
Written informed consent provided	Pregnancy
*FARS functional stating score of ≤ 5 and a total mFARS score of ≤65 on enrolment	

*FARS, Friedreich’s Ataxia Rating Scale; mFARS, Modified Friedreich’s’ Ataxia Rating Scale.

Control participants must meet the following criteria: age > 5 years and be able to provide written informed consent. Control participants will be excluded if they have any MR contraindications, are pregnant, or present with any diagnosed medical and neurological condition which may interfere with the conduction of the study.

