**Fig 1 pone.0269649.g001:**
[figure not shown]
Summary of TRACK-FA study procedures according to participant age. The testing schedule varies according to age. All participants will also undergo a speech assessment, whilst all FRDA participants will undergo additional clinical testing.

*Collection of medical and demographic information*. Medical history specific to FRDA will be taken in the enrolment session for all participants with FRDA. The following information will be collected: the length of *FXN* GAA repeat expansions on the smaller (GAA1) and larger (GAA2) allele, the type of mutation detected, age of symptom onset including first symptom, disease duration, presence of diabetes and medical information pertaining to nervous system disorders (apart from FRDA), heart conditions, vision impairments, skeletal abnormalities (scoliosis and foot deformities), hearing conditions, bowel and bladder conditions, presence of inflammatory diseases, details on concurrent trial participation and COVID-19 status.

The following information will be collected for all participants: height and weight (used to calculate body mass index (BMI), and medications (prescription/non-prescription).

*MRI scanning to assess primary outcomes*. All participants will undergo brain and (cervical) spinal cord imaging procedures lying supine in a three tesla (3T) MRI scanner (Siemens Skyra, Siemens Prisma or Philips Ingenia). Significant effort has been made to ensure harmonisation of MR protocols across all the sites with vigorous testing of the imaging sequences prior to the commencement of the study. The inclusion of QSM, diffusion MRI and MRS in the procedure allows for the quantification of iron accumulation, microstructural and neurochemical profile of areas pertinent to disease pathology [39], potentially providing further insights into neuronal damage and gliosis associated with the neurodegenerative nature of this disease [32].

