#### Assessing the longitudinal changes over time

The within-person longitudinal slopes across the multiple visits will be estimated using a mixed linear model in which the slope for each participant is treated as a random effect. Within this framework we will assess the significance of a fixed effect that captures the difference in mean slope for individuals with FRDA with respect to controls. Due to the participant demographic in this study the analysis of within person slopes can give an indication of how age of onset and disease stage/severity can influence the subsequent clinical changes that occur within the parameters of participant demography.

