#### Interim analyses and accounting for missing data

Interim analysis will be performed after the completion of each visit (baseline, 12-month and 24-month time points). There are likely to be instances of missing data in this study, due to the study requiring interstate travel to attend testing, participant health concerns and normal participant dropout. We had increased our target sample size by 25% to account for 20% anticipated participant attrition, and if required the consortium will consider the recruitment of additional participants in order to ensure that the analysis has the necessary statistical power. Participants with missing data for just one of the three visits will be included under a missing at random assumption for longitudinal mixed linear modelling.

*Data confidentiality and storage*. Participants’ personal information, genetic information, clinical, cognitive, mood and biospecimen data generated in this study will be de-identified by assigning a unique study identification number. All raw, pre-processed (defaced) and processed MRI images will be stored in the Monash XNAT platform [78]. Defacing of 3D T1 and T2 MRI data will be conducted using MaskFace [79] version 10.15.18 [80]. To ensure consistency, the team at the University of Minnesota provided each site with a Docker or Singularity container containing scripts to automatically sort the data and deface the brain T1 and T2 images before upload to XNAT [78]. The REDCap database (Helix, Monash University) [81] will be used to store all other study data. All paper-based case report forms (CRFs) will be kept in a locked cabinet to be accessed by authorised personnel at each site according to the Good Clinical Practice guidelines. Data entry into REDCap will follow standard double data entry processes, with responsibility for accuracy lying with individual sites. The central study coordinator will provide overall oversight of data management through randomised checks of a proportion of REDCap entries.

Academic sites and industry collaborators will have secure access to both raw and processed data within the Monash XNAT and REDCap platforms throughout the duration of the study in accordance with the study agreements. Data may also be made available to third parties at the completion of the study, and upon request, provided that they obtain approval from the TRACK-FA Steering Committee. All records and samples will be stored according to local IRB requirements at each site.

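### The imaging slope model names no severity term while relying on missing at random, so the FRDA mean slope is open to bias, of either sign, if missed scans depend on disease severity

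*Protocol article*

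**What the plan says.** All references are to the protocol article.

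- *Assessing the longitudinal changes over time*: slopes are "estimated using a mixed linear model in which the slope for each participant is treated as a random effect", and the tested fixed effect is the FRDA-control difference in mean slope. No severity, onset or genotype term is named.
- *Interim analyses and accounting for missing data*: those who miss a single visit out of three "will be included under a missing at random assumption for longitudinal mixed linear modelling". Expected causes of loss are travel, "participant health concerns and normal participant dropout". The stated protection is a 25% larger sample for 20% attrition, with possible extra recruitment.
- *Stratification of participants*: people earlier in the disease, especially those still walking, are said to progress faster.
- *Introduction*: dentate iron is said to change faster as the disease advances, while dentate atrophy is fastest early and then levels off.
- *Adjustment for potential site differences*: disease severity is a fixed effect, but in the baseline site model only.
- *Inclusion and exclusion criteria*, Table 1, excludes people with "MR contraindications (e.g., pacemaker or other metallic surgical implants"). The *Introduction* states: "Non-neurological features include cardiomyopathy, visual and hearing impairments, diabetes mellitus, glucose intolerance and skeletal deformities". Medical history at enrolment covers "heart conditions, vision impairments, skeletal abnormalities (scoliosis and foot deformities").

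**The concern.** A likelihood mixed model under missing at random is valid when the chance of losing a scan depends only on what the model contains. As described, that is group, time and the scans already obtained. One or two earlier scans say little about a participant's stage. If stage drives both the loss of a scan and the rate of change, the participants still scanned differ in slope from those enrolled, and the model corrects for this only in part.

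The article itself supplies half of this chain, because it links rate of change to stage. It supplies part of the other half by expecting loss for health reasons. Controls have no disease stage, and those with an interfering medical or neurological condition are excluded, so the effect would not be expected to cancel in the FRDA-control contrast.

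Objective 1 uses that contrast to find the biomarkers most sensitive to change. On the article's own description, losing more advanced participants would understate the change in dentate iron and overstate dentate atrophy. Bias that differs in sign between biomarkers can affect their ranking, not only their size.

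**Working it through.** **The plan's own figure.** 1/(1 − 0.20) = 1.25, so 25% more participants for 20% attrition is right. 140 × 1.25 = 175; the article selects 200, and 200 × 0.8 = 160 remain. This protects power. It does nothing about bias from selective loss.

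**Model for the check.**
- Imaging value at year t (0, 1, 2): y = b + s·t + e.
- Slope: s = μ − σ_s(ρS + √(1 − ρ²)·z), where S is baseline severity in SD units.
- Loss of scanning in each year: logit P = a + ln(OR)·S, with no return once lost.
- Fit: generalised least squares with known variance components, all observed scans used, S left out.

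**Assumed inputs (none given in the article).** In units of the baseline imaging SD: σ_s = 0.3 per year, residual SD 0.3. Correlation of S with baseline imaging 0.5; ρ of 0.3-0.5 in size; OR 2 or 4 per SD; 8-16% of scans lost by Visit 3.

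**Tying the slope to the planning effect.** SD of the 24-month change = √((2 × 0.3)² + 2 × 0.3²) = √0.54 = 0.735. At d = 0.3 (*Sample size calculation*), the mean slope is 0.3 × 0.735/2 = 0.110 per year.

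**Bias of the FRDA mean slope at d = 0.3, as a percentage of the true slope.** The ranges run over |ρ| = 0.3 to 0.5.

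| Scans lost | OR per SD | Lost participants change faster (toward zero) | Lost participants change more slowly (away from zero) |
|---|---|---|---|
| about 8% | 2 | 3-5% | 2-4% |
| about 8% | 4 | 5-9% | 4-7% |
| about 15-16% | 2 | 6-9% | 4-8% |
| about 15-16% | 4 | 10-16% | 7-13% |

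The first bias column is at about 15% lost in its lower rows. A repeat run at exactly 16% gave 17% in the last cell, so the upper end is approximate.

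**Dependence on the mean slope.** The absolute bias does not depend on μ, so the percentage scales with 1/μ. With μ = 0.3 per year, d = 0.6/0.735 = 0.82 and the percentages shrink by 0.110/0.3 = 0.37. Runs at that slope gave 1.6-4.5% toward zero at 10% loss and 2.8-7.8% at 20% loss. With ρ = −0.3, across 5-20% loss, the bias was 0.6-3.1% away from zero.

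**When there is no problem.** With loss unrelated to S, bias was below 1%. With ρ = 0, it was at most about 1%.

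**With S and S-by-time in the model, evaluated at mean S:** within about 1% of the truth in every setting.

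**Comparison with sampling error.** At d = 0.3 the relative standard error of the FRDA mean change is 1/(0.3√200) = 0.24 with 200 participants and 1/(0.3√160) = 0.26 with 160, so about 25%. The bias is below one standard error throughout the table.

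**The case against.** The strongest reply is that missing at random in a mixed model is a standard default, that an article condenses its model to the main terms, and that covariates and sensitivity analyses may sit in a fuller plan. Nothing in the article says that severity is barred from the slope model. This stands, and it is why the point is an improvement and not an error. What remains is that the article has its own analysis section. It names severity as a covariate in one model and not in this one, and it states the missing-data assumption for this one.

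Some stronger readings are tempting, and the article does not support them:

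- *A reader might infer that cardiac devices or spinal surgery remove FRDA participants from MRI during follow-up.* The article lists cardiomyopathy and skeletal deformities as disease features and implants as an enrolment exclusion. It does not say that such devices follow enrolment, or how often. The concern does not need this route, since health-related loss of any kind may depend on severity.
- *A reader might infer that the FRDA slope is biased.* Bias needs loss that depends on severity beyond what the earlier scans show, and the article gives no such evidence.
- *A reader might infer that severity data are collected and left unused.* Severity enters the site model. Onset, GAA length and duration enter the baseline correlations and the stratified analyses, and slopes are to be read against onset and stage. Those analyses do not change the overall slope contrast or its missing-data assumption.
- *A reader might infer a shortfall near a quarter of the slope.* With 16% lost and a correlation of 0.5, a 24% shortfall takes an odds ratio somewhere around 8-20 per SD, which is very strong selection. A loss of 16% would also assign most of the planned 20% attrition to severity-driven loss.

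**Conclusion.** The point holds in conditional form. The slope model as described rests on missing at random given group, time and earlier scans. The article's own remarks on stage and on health-related loss make that doubtful. If scan loss depends on severity, the FRDA mean slope is open to bias of roughly 2-16% at d = 0.3, toward or away from zero according to how each biomarker's rate varies with stage. This rests on the assumed 8-16% loss, odds ratio of 2-4 per SD and correlation of 0.3-0.5 in size. It is smaller for measures with a larger mean slope relative to its SD, and close to nil if loss or slope is unrelated to severity. The bias is below the sampling error of about 25%, but it can run in opposite directions for the biomarkers being ranked, and a larger sample does not reduce it.

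**What to change.** In the longitudinal imaging model:

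1. Add baseline severity (mFARS or FARS stage) and its interaction with time within FRDA. Centre it at the mean of the enrolled FRDA participants and set it to zero for controls, so that the group slope contrast keeps its meaning. Using the same variables as auxiliary variables in an imputation of missed scans is an alternative.
2. Include every participant with at least one scan. The present sentence covers only those missing a single visit, so a participant with Visit 1 alone falls outside it. In the simulations, keeping or dropping such participants moved the bias by less than 2 percentage points, so this is mainly for a clear rule.
3. Report one sensitivity analysis that shifts the slopes of participants with missed scans over a stated range.

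The cost is a few extra parameters, a short change of wording and one further analysis. The severity measures are already collected, and little or no precision is lost.

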### Status and timeline of the study

TRACK-FA participant recruitment will occur throughout the period of January 2021 to October 2022. As of September 2021, total of a total of 27 individuals with FRDA consisting of 21 adult participants with FRDA, five older paediatric participants with FRDA and 1 younger paediatric participant with FRDA, have been tested. A total of 11 control participants have been tested.

The target recruitment statistics for the 18-month period will include a total of 200 participants with FRDA, including 110 adult participants with FRDA, 82 participants with FRDA of age 11–17 and eight total participants of age 5–10 (Fig 2).

**Fig 2 pone.0269649.g002:**
[figure not shown]
Summary of recruitment statistics across seven international study sites for the TRACK-FA study. The target recruitment and the cumulative total of FRDA and control participants currently recruited into the study (categorised into the age groups) have been indicated.

#### COVID-19 impact

The TRACK-FA study has been hindered in its progression due to the COVID-19 global pandemic. Minimising the risk of exposure to COVID-19 for individuals with FRDA has created challenges in a study that depends on face-to-face contact. Site-specific lockdowns, differing vaccination uptake and COVID-related reluctance to travel have also severely limited recruitment. To date, the recruitment targets remain unchanged, and the study is proceeding with a six-month extension for enrolment and assessments as part of visit 1.

## Discussion

There is an urgent need to develop biomarkers for FRDA that can help in the design and monitoring of clinical trials. Specific anatomic targets in the brain and the spinal cord may be more or less relevant at different stages of disease progression while biomarkers that can monitor the pharmacodynamic effects and disease progression are needed as outcome assessments [15, 38, 82]. Neuroimaging outcome measures show great promise in this area, however further work is needed to fully understand the relationship between the neuroimaging outcome measure and disease progression. TRACK-FA is a multimodal, multicentre, longitudinal study which aims to accelerate the discovery of clinical-trial ready biomarkers of disease progression to support this unmet need.

The multicentre nature of the study allows a wider and larger demographic of individuals with FRDA with varying disease severities to be captured, overcoming one of the biggest hindrances faced in biomarker research in rare diseases. Importantly, this large cohort will facilitate targeted subgroup analysis of sufficient statistical power to tease apart the relationship between the underlying neuropathology, and parameters such as clinical presentation, age of onset, age, and genotype. This information will not only guide the validation of neuroimaging biomarkers providing a pre-harmonised set of FRDA imaging centres, which can be used in future trials, but also inform drug development strategy by identifying regions that should be targeted by interventions for maximum impact within a given cohort.

TRACK-FA uses a combination of harmonised MRI modalities to create a unique imaging protocol. The multi-modal combination of brain and spinal cord structural MRI, QSM, diffusion MRI and MRS will allow us to determine the extent, timing and effect size of changes that occur in the brain and the spinal cord with each modality disease progression with higher precision [37]. Moreover, the harmonisation of these modalities will allow for validation of results across different sites and scanners. This will lead to an increased robustness of the biomarkers and their pertinence to detect real change in a potential therapeutics pharmacodynamic effect and/or disease progression, adding to their “clinical trial readiness”. These chosen outcome measures have shown great promise to monitor the effects of neuronal damage and gliosis associated with neurodegeneration [83] and provide an opportunity to obtain an holistic image of disease progression at multiple levels of the brain and spinal cord. For example, in the brain the outcome measures will include iron levels within the dentate nuclei [40], volumetric changes in a range of brain substructures [15, 16], and microstructural alterations in the orientation and organisation of white matter fibres [83]. In the spinal cord, the outcome measures will include the cross-sectional area of the cervical spinal cord, diffusion parameters in the white matter [15, 39] and the ratio of key metabolites, such as N-acetyl aspartate and myo-inositol [83].

In addition to neuroimaging measures, TRACK-FA will collect clinical, cognitive, mood, speech and blood biomarker measures of disease progression. Correlation between these outcome measures will be used to understand the functional utility of specific neuroimaging biomarkers for tracking disease progression and their clinical relevance. This data can also be used individually to evaluate disease associated temporal changes and measure the clinical efficacy of current and future therapeutics aimed towards the improvement of cognition and mood as well as dysarthria in FRDA. Furthermore, the proposed subgroup analysis, allows us to determine how factors such as age of onset and GAA repeat size, correlate to neuroimaging measures, and how each of these factors contribute to FRDA neuropathology [24, 84] contributing to the possible development of therapeutic targets specific for age of onset.

TRACK-FA will accelerate the drug discovery pipeline in a climate where urgency is required for clinical trial-ready biomarkers. A clinical trial-ready biomarker must be reproducible and robust to changes in variables [85, 86]. In this study validation of biomarkers is achieved through several different methods, including a multicentre approach, independent imaging analysis performed by IXICO, control of MRI scanner differences, and the relationship of neuroimaging measures to functional and biospecimen measures. This use of a harmonized and multicentre approach aims to deliver a large multi-modal neuroimaging dataset which in the future can be used to assess the variability and generalizability of finding across studies, more robustly inform future clinical trial design and serve to combine with prospectively acquired interventional data enhancing the statistical power of future studies [87, 88].

